#### Secondary outcomes

In addition to testing past-month abstinence as the primary outcome, we will also test a more stringent operationalisation of abstinence—continuous abstinence since discharge, as measured at the 3-month follow-up—as a secondary outcome. Comparison of groups, in terms of proportion of participants reporting continuous abstinence, will be analysed using a Pearson’s chi-square test. Approach bias will be analysed using mean AAT score, with the end-point being after session 6 of ABM. Change in AAT score between baseline and session 6 will be analysed using a linear mixed-effect model (LMM) testing the main effects of group and time, and their interaction.

Methamphetamine craving will be analysed using mean scores on the frequency and strength scales of the CEQ, with end-points including post-training (session 6), 1-month, and 3-month follow-ups. Two separate LMMs (one for the CEQ frequency scale, and one for the CEQ strength scale) will be used to analyse reduction in scores at these end-points, relative to score at baseline. Both LMMs will test the effect of group, time (4 levels: baseline, post-training, 1-month follow-up, and 3-month follow-up), and the interaction between these 2 effects.

MUD severity will be indexed using mean scores on 2 different measure—the SDS and SCID-5-RV. End-points for this outcome are the 1-month follow-up (SDS only) and at the 3-month follow-up (both SDS and SCID-5-RV). Separate LMMs for each measure will be used to test change in score, relative to baseline. Both LMMs will test the effect of group, time, and their interaction, although for SDS, time will have 3 levels (baseline, 1-month follow-up, 3-month follow-up), while for SCID-5-RV, it will only have 2 levels (baseline, 3-month follow-up).

For MUD severity, binary categories will also be derived from each of the measures used. For SCID-5-RV, participants will be classified according to whether they meet MUD criteria at the 3-month follow-up. For SDS, participants will be classified according to whether they have a score of 5 or more at each end-point. For each of these measures, proportions of participants in each category will be compared between groups using Pearson’s chi-square. Time to first lapse (i.e. number of days between discharge and first methamphetamine use, measured using a single question incorporated into the TLFB interview at both follow-ups) will be compared between groups using Cox regression analysis. Acceptability of the intervention following the final session of ABM will be assessed using EDS descriptive statistics (mean, standard deviation).

Pearson’s correlation tests will be used to examine the association between impulsivity and approach bias. Separate logistic regression models, testing each dimension of impulsivity, along with group and the interaction term between group and the impulsivity dimension, will be used to explore which dimensions of impulsivity moderate the effectiveness of ABM on abstinence from methamphetamine. LMM will be used to explore whether any dimensions of impulsivity moderate the effect of ABM on continuous outcomes.

The primary analyses will be conducted on an intention-to-treat basis, whereby attempts will be made to follow-up everyone who commences a single session of training. Missing outcomes (i.e. from those lost to follow-up) will not be imputed in the primary analysis, though supplementary sensitivity analyses of past-month and continuous abstinence will be conducted in which we will assume all those lost to follow-up used methamphetamine. Additional “per-protocol” supportive analyses will be restricted to participants who completed at least 4 full sessions of training, and to those who completed all 6 sessions.

All statistical analyses will be conducted by an unblinded statistician who is not involved in participant recruitment or data collection. Interim analyses conducted or supervised by the unblinded statistician are permitted for the purpose of any reports (e.g. student projects, reports to the funding body) that are due prior to completion of the project. These analyses will be accessible to the chief investigator and any other relevant personnel (e.g. the student and their supervisor, in the case of a student report). The trial will end when we have recruited 100 participants—there is no intention to stop the trial in response to interim analyses.

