## Methods

### Aims

Our primary objective is to test whether 6 sessions of “personalised” ABM, relative to a “sham training” control condition, increases the likelihood of past-month abstinence from methamphetamine 1 month and 3 months after discharge from rehabilitation. As a secondary measure of efficacy, we will also test whether ABM increases the rate of continuous abstinence over the whole 3-month follow-up period.

Other secondary objectives include:
Testing whether ABM reduces methamphetamine approach bias, relative to sham training.Testing whether ABM reduces methamphetamine craving, relative to sham training.Testing whether ABM reduces severity of MUD after discharge from rehabilitation, relative to sham training.Testing whether ABM delays the time to first lapse to methamphetamine use after discharge from rehabilitation, relative to sham training.Testing whether dimensions of impulsivity, particularly positive and negative urgency, correlate with methamphetamine approach bias, and whether they moderate the effect of ABM on methamphetamine use, dependence symptoms, and approach bias.Measuring the acceptability of this novel ABM training task.

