#### Substance use

A timeline follow-back (TLFB) interview [36] is used to confirm eligibility and measure frequency and quantity of methamphetamine use and route of administration. To aid description of the sample, information regarding tobacco, alcohol, and other illicit/non-prescribed substance use is also recorded using the TLFB. Time frames covered by the TLFB are as follows: the 28 days prior to commencing residential treatment (at baseline), the 28 days following discharge from residential treatment (1-month follow-up), and the past 28 days (3-month follow-up).

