One and 3 months following discharge from rehabilitation, a researcher not involved in administering training (and therefore blind to treatment condition) phones the participant and administers the TLFB, CEQ, and SDS. At the 3-month follow-up, the SCID-5-RV is also administered. We also assess continuous abstinence since discharge with a categorical (yes/no) question regarding any illicit amphetamine use since the previous follow-up and, if any has been used, the date of first use is assessed to allow survival analysis of time to first lapse. One-month follow-ups will occur no earlier than 28 days after discharge, and may be conducted up to 56 days post-discharge. Three-month follow-ups may be conducted no earlier than 84 days (i.e. 12 weeks) post-discharge and may be conducted up to 150 days post-discharge. Participants are sent a $20 supermarket gift card for each follow-up completed. At the 3-month follow-up, we also ask participants “Do you believe you received the form of training intended to reduce impulses to approach drugs or do you believe you were in the placebo group who received a form of training that was not designed to reduce approach impulses?” to assess blinding.

In accordance with intention-to-treat principles, we attempt to follow up all participants who are randomised (i.e. who commence the first session of ABM training), regardless of how many sessions they complete, unless they withdraw from participation. If a participant tells a researcher that they wish to withdraw (or if they tell clinical staff at the residential facility, and this is communicated to a member of research staff) the researcher seeks to ascertain their reason for withdrawal and communicates this to the study coordinator, so that the reason for withdrawal can be recorded. Reasons for withdrawal are classified according to whether they are related to the acceptability of the study protocol (e.g. finding the ABM training or questionnaires distressing) or are unrelated (e.g. the participant simply losing interest in participating, or facing stressors unrelated to study participation).

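### Continuous abstinence is read at a call made anywhere from day 84 to day 150, with no common cut-off day and no stated rule for combining the two follow-up answers

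*Protocol article*

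**What the plan says.** All references are to the Methods of the protocol article.

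- **Aims:** the secondary efficacy question is whether "ABM increases the rate of continuous abstinence over the whole 3-month follow-up period".
- **Secondary outcomes:** the outcome is "continuous abstinence since discharge, as measured at the 3-month follow-up", compared by Pearson's chi-square test.
- **Procedure, measurement:** continuous abstinence since discharge is assessed with "a categorical (yes/no) question regarding any illicit amphetamine use since the previous follow-up". If there was any use, "the date of first use is assessed to allow survival analysis of time to first lapse".
- **Procedure, timing:** the 1-month call may be made from day 28 to day 56. The 3-month call may be made no earlier than day 84 and "may be conducted up to 150 days post-discharge". Table 1 gives 12 weeks as its expected time.
- **Substance use:** the 3-month timeline follow-back covers only the preceding 28 days.
- **Secondary outcomes, time to first lapse:** this is "measured using a single question incorporated into the TLFB interview at both follow-ups" and analysed by Cox regression.
- **Secondary outcomes, missing data:** "Missing outcomes (i.e. from those lost to follow-up) will not be imputed in the primary analysis". The same sentence adds sensitivity analyses of past-month and continuous abstinence that count everyone lost as having used.

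**The concern.** The probability of remaining abstinent falls with time. A yes/no outcome read on whatever day the participant is reached therefore mixes different lengths of exposure. Someone called on day 84 has to stay abstinent for 84 days to count as a success; someone called on day 150 has to do so for 150 days. The reported proportion then depends partly on how quickly people answered the phone, and it does not estimate the three-month quantity in the aims.

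The second issue is the look-back. For anyone interviewed at 1 month, the 3-month item starts at that interview (day 28 to 56), not at discharge. The 28-day timeline follow-back cannot recover an earlier lapse. If the 3-month answer were used alone, a participant who used in the second week and then stopped would be classed as continuously abstinent, while counting as an event in the Cox model. The text does not state how the two answers are joined, nor what look-back applies to someone who missed the 1-month call.

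**Working it through.** The article gives no expected rate or power for this outcome, so there is no such figure to reproduce. Its day count is consistent: 84 / 7 = 12 weeks.

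**1. Window.** 150 − 84 = 66 days; 150 / 84 = 1.79.

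**2. Effect of call date on the proportion.** The Background cites 47% using within 3 months and 78% within 1 year of starting residential rehabilitation. Assumption: these rates apply from discharge. Fit a Weibull curve, S(t) = exp(−λt^k), through S = 0.53 at 3 months and S = 0.22 at day 365.

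- 3 months taken as 91.3 days: k = ln(ln 0.22 / ln 0.53) / ln(365/91.3) = 0.63; S(84) = 0.547, S(150) = 0.420; difference 12.7 points.
- 3 months taken as 84 days: k = 0.59; S(84) = 0.53, S(150) = 0.41; difference about 12 points.
- Other curves anchored at 91.3 days: piecewise exponential 0.558 to 0.439 (12 points); a single exponential through the 3-month figure only, 0.558 to 0.352 (21 points).

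These compare everyone called on day 84 with everyone called on day 150. For a between-arm bias, what counts is the difference between arms in the share called late. On the Weibull curve, each 10-percentage-point difference in the share called on day 150 rather than day 84 shifts the comparison by 0.10 × 12.7 = 1.3 points. With 50 per arm and no loss, the standard error of the difference is about √(2 × 0.53 × 0.47 / 50) = 10 points.

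**3. Look-back, if the 3-month item were used alone.** On the exponential curve, 17.7% have lapsed by day 28 and 32.3% by day 56. The share q of these who report no later use is not in the document; assume 10% to 40%. Apparent abstinence = 0.53 + q × early lapsers.

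- 1-month call at day 28: 0.53 + 0.10 × 0.177 = 0.55, up to 0.53 + 0.40 × 0.177 = 0.60.
- 1-month call at day 56: 0.56 to 0.66.

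If both answers are combined, the figure stays at 0.53.

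**4. Loss to follow-up.** The pilot lost 45% by 3 months (Discussion). Take true abstinence of 53%, 17.7% lapsed by day 28, and all early lapsers reached at 1 month.

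- Complete cases, loss unrelated to lapse: 53%, no bias.
- Complete cases, early lapsers lost more often (60% against 35%): 0.3445 / (0.3445 + 0.190 + 0.071) = 57%.
- Known lapsers counted as failures and all other lost participants dropped, 45% random loss: 0.2915 / (0.2915 + 0.161 + 0.177) = 46%, seven points too low.
- Kaplan-Meier with everyone reached at 1 month: 0.823 × (0.53 / 0.823) = 53% in both loss scenarios, because the early lapse is already an observed event and later loss is taken as unrelated to later lapse.

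**The case against.** The strongest reply is that the outcome is explicitly defined from discharge, and that the lapse question is put at both calls. Chaining the 1-month answer to the 3-month answer gives exactly abstinence since discharge. A reader might infer that the plan classes early lapsers as abstinent; it does not say so. That happens only if a recorded 1-month answer is ignored. What stands is that the joining rule is not written, and that the outcome is described as measured at the later call.

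A reader might also infer that known lapses are discarded as missing and that the abstinence rate is therefore inflated. No sentence says how a participant who reports a lapse at 1 month and is then lost is handled in the main analysis, and the planned sensitivity analysis counts every such person as a user. Nor is inflation of 3 to 10 points supported. It comes from taking 55 completers at 50% and adding 4 to 14 known lapsers to the denominator (27.5/55 = 50% to 27.5/59 = 46.6% or 27.5/69 = 39.9%) while adding none of the lost non-lapsers. If loss is unrelated to lapse, the overstatement is zero. The 57% scenario shows about 4 points, under assumed differential loss.

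On the window, the follow-up callers are blind, Table 1 expects the call at 12 weeks, and the Cox analysis can handle unequal follow-up by censoring. These points reduce the likely effect. They do not supply a common cut-off for the binary outcome.

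**Conclusion.** The window point holds on the text: one binary outcome, exposure of 84 to 150 days, no fixed day. Its main effect is noise and a proportion that does not estimate the stated three-month quantity. Bias between arms requires call timing to differ by arm, which nothing in the document shows. The 12 to 13 point swing is an outer illustration resting on a fitted curve and on rates counted from the start of rehabilitation.

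The look-back point holds in a narrower form: the 3-month item alone would not measure the outcome, and the combination of answers is left unstated. The text does not support calling the outcome biased upward as written.

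This falls below a must-fix. The outcome is secondary, and neither the look-back nor the handling of lost lapsers touches the primary outcome, which comes from the 28-day timeline follow-back.

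**What to change.** Define the outcome as no methamphetamine use from discharge to day 84, derived from the answers and dates of first use at both interviews combined. A lapse reported at 1 month then always counts as a lapse, and first use after day 84 does not. Say also what look-back applies when the 1-month call was missed.

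Set the rule for participants not interviewed on or after day 84 at the same time. Do not count only their known lapses as failures and drop the rest, which pulls the rate down. Use a method that handles both groups, for example a Kaplan-Meier estimate of abstinence at day 84 per arm with censoring at the last interview. This assumes that, after that interview, loss is unrelated to later lapse. Keep the planned analysis that counts all lost participants as users as the check on that assumption.

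The cost is a few sentences in the analysis text; the dates are already collected. The downside is that lapses between day 84 and a late call no longer count in this outcome, though they remain in the Cox analysis.

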#### Approach bias

Participants complete a computerised approach-avoidance task (AAT) to measure approach bias. We use a relevant-feature version of the task as this may achieve a more reliable measurement of approach bias than irrelevant-feature tasks. As described by Kersbergen, Woud, and Field [39], this is the only version of the AAT that has thus far been shown to have acceptable internal consistency (Cronbach’s alpha = .70 in an alcohol version of the task). Thus, participants are presented with 2 blocks of 80 randomised images (the same 20 methamphetamine-related and 20 positive images in each block, each presented twice in each block) on a laptop computer screen. For both classes of images, 10 are a set of pictures (same for all participants) used only in the AAT. The remaining 10 are the most highly rated of the remaining 40 pictures that are also used in the ABM training.

In the first block, participants are instructed to push a joystick in response to methamphetamine-related pictures and pull the joystick in response to positive images. In the second, these instructions are reversed, so that participants are required to pull the joystick in response to methamphetamine-related images and push in response to positive images. Pushing the joystick causes the image to shrink until it disappears, creating the impression of the image “receding” into the “distance”, as if pushing the joystick has actually “pushed” the image “away”. Pulling the joystick causes the image to increase in size until it is double the height and width of its original display (i.e. filling as much of the screen as possible, while still displaying the whole image) when the joystick is pulled to the maximum extent, creating the impression of “approach”, as if pulling the joystick has “pulled” the image “towards” the participant. Thus, for each image included in the AAT, participants perform an “approach” action twice in one block and an “avoidance” action twice in the other block.

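### The five secondary LMMs estimate a group difference at a pre-randomisation baseline, which leaves the tests unbiased but less precise than the same data allow

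*Protocol article*

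**What the plan says.** The Secondary outcomes section of the protocol article fixes five linear mixed models.

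- AAT: the score change from baseline to session 6 "will be analysed using a linear mixed-effect model (LMM) testing the main effects of group and time, and their interaction".
- CEQ frequency and CEQ strength: "Both LMMs will test the effect of group, time (4 levels: baseline, post-training, 1-month follow-up, and 3-month follow-up), and the interaction between these 2 effects".
- SDS and SCID-5-RV: "Separate LMMs for each measure will be used to test change in score, relative to baseline". The section adds that "for SDS, time will have 3 levels (baseline, 1-month follow-up, 3-month follow-up"), while for SCID-5-RV "it will only have 2 levels (baseline, 3-month follow-up").

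In each model baseline is part of the outcome and group has its own effect there. No equal-baseline constraint and no baseline covariate is stated.

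On timing, the Allocation section puts randomisation at the start of the first training session. The Procedure section puts the SCID, SDS, CEQ and AAT before that session. Table 1 lists the CEQ and AAT in the session 1 column, but the Procedure text orders them ahead of training, so all the baselines precede randomisation.

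**The concern.** Before randomisation the two arms are samples from one population, so any baseline gap between them is chance. A model with a free group effect at baseline estimates that gap and subtracts all of it from the follow-up difference. The efficient amount to subtract is only the part that predicts follow-up.

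The Sample size section says that the target of 100 was set by feasibility, without a power calculation, and that the trial is partly meant to supply effect sizes for later trials. With the sample fixed, the analysis model is one of the few remaining ways to gain precision. At stake is the width of the intervals for approach bias, craving and MUD severity.

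**Working it through.** There is no power figure in the plan to reproduce.

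**Inputs from the protocol article:** 100 participants allocated 1:1, hence n = 50 per arm (Sample size; Allocation). In the pilot, 55% completed the 3-month follow-up (Discussion) and 62% completed the full training course (Background).

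**Assumed, not in the documents:** ρ, the baseline-to-follow-up correlation, from 0.3 to 0.7; k, the ratio of baseline SD to follow-up SD, of 1 or 0.5; a true difference of 0.5 follow-up SD; two-sided 5% tests. Variances are in units of the squared follow-up SD.

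**Step 1: complete data, k = 1.** The variance of the arm contrast at one end-point is

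- planned (free baseline): 2 × 2(1−ρ)/n
- common baseline mean: 2(1−ρ²)/n
- ratio: (1+ρ)/2

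| ρ | Planned | Common baseline | Ratio | Power | n per arm for 80% power |
|---|---|---|---|---|---|
| 0.3 | 0.0560 | 0.0364 | 0.65 | 56% → 75% | 88 → 58 |
| 0.5 | 0.0400 | 0.0300 | 0.75 | 71% → 82% | 63 → 48 |
| 0.7 | 0.0240 | 0.0204 | 0.85 | 90% → 94% | 38 → 33 |

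Ignoring baseline altogether gives 2/50 = 0.040. With equal SDs and complete data, the planned contrast is therefore noisier than no baseline at all when ρ is below 0.5.

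**Step 2: dropout, k = 1.** Let m per arm have the follow-up value and r = m/n. Participants with only a baseline stay in the LMM, which gives

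- planned: 2[(1−ρ²)/m + (1−ρ)²/n]
- common baseline: 2(1−ρ²)/m
- ratio: (1+ρ)/[(1+ρ) + r(1−ρ)]

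At r = 0.62 (m = 31) and ρ = 0.3, the variances are 0.0783 and 0.0587, a ratio of 0.75. At ρ = 0.5 they are 0.0584 and 0.0484, a ratio of 0.83.

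At r = 0.55:

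- ρ = 0.3: 1.3/(1.3 + 0.385) = 0.77; power 40% → 49%
- ρ = 0.5: 1.5/(1.5 + 0.275) = 0.85; power 50% → 57%
- ρ = 0.7: 1.7/(1.7 + 0.165) = 0.91; power 70% → 74%

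**Step 3: unequal SDs, complete data.** The ratio becomes (1−ρ²)/(1 + k² − 2ρk). At k = 0.5:

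- ρ = 0.3: 0.91/0.95 = 0.96
- ρ = 0.5: 0.75/0.75 = 1.00
- ρ = 0.7: 0.51/0.55 = 0.93

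**Step 4: three or four time levels.** With equal SDs and a common correlation, the ratio for each single end-point contrast is again (1+ρ)/2. The interaction itself becomes a joint test on 2 or 3 degrees of freedom. For a constant 0.5 SD effect at ρ = 0.5 and complete data, its power goes from 74% to 90% with three levels and from 73% to 92% with four.

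**Check.** In an artificial two-time-point data set with complete data and ρ = 0.5, the LMM interaction was −0.3859 (SE 0.1823), identical to the difference in mean change. On the same data the SE was 0.168 with baseline as covariate and 0.159 with a common baseline mean. Over 4,000 simulated trials the variance ratio of covariate adjustment to change score was 0.752, against 0.75 in theory. The planned model was not more precise in any scenario examined.

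**The case against.** The planned models are valid. They test what the article says they test, change relative to baseline, without bias. They concern secondary outcomes only, since the primary outcome is a chi-square comparison of abstinence. The article makes no power claim that this could contradict. All of that stands and limits the weight of the point.

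A reader might also infer more than the documents support:

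- **That all five interactions are change-score comparisons.** The identity is exact only with two time points and complete data. CEQ has four levels and SDS three. With dropout the LMM also uses baseline-only participants, which reduces the loss.
- **That the AAT is known to have a low ρ.** The article calls its task format "the only version of the AAT that has thus far been shown to have acceptable internal consistency", with a Cronbach's alpha of .70 from an alcohol version. That describes consistency within one sitting and is not a test-retest correlation.
- **That restricted severity baselines make the loss worse.** If restriction makes the baseline SD smaller than the follow-up SD, the loss shrinks (step 3). The entry threshold of 4 criteria applies directly to the SCID count, and SDS is not an entry criterion.
- **That the pilot rates forecast this trial.** The 62% is completion of four sessions during withdrawal treatment, and the authors expect better retention here. The 55% and 62% rows are illustrations.

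The objection that such detail belongs in an unseen analysis plan does not remove the point, because the article states the models and their time levels.

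**Conclusion.** The point holds as a loss of efficiency in five secondary analyses. The free baseline group effect serves no purpose in the intention-to-treat comparison. Removing it leaves 0.65 to 0.85 of the planned variance for ρ from 0.3 to 0.7 if SDs are equal and data complete, 0.77 to 0.91 at 55% retention, and 0.93 to 1.00 if the baseline SD is half the follow-up SD. The direction follows from the design, but the size rests on ρ and the SD ratio, which the documents do not give. The gain is best supported for AAT and CEQ and may be near nil for SCID-5-RV.

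The documents do not support reading this as bias, as invalid tests or as a fault in the primary analysis. The impulsivity moderation LMMs are not described in enough detail to judge.

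**What to change.** In Secondary outcomes, for the intention-to-treat analyses of all five measures, do one of two things:

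- constrain the baseline mean to be equal across arms, keeping time and group-by-post-baseline-time terms and dropping the baseline group effect; or
- model the post-baseline scores with baseline as a covariate.

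Include site, because randomisation is stratified by it. Report the adjusted arm difference with its 95% CI at each named end-point; this also serves the stated aim of supplying effect sizes.

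In the per-protocol subsets (at least 4 sessions; all 6 sessions), use baseline as a covariate and not the equal-baseline constraint. Those subsets are selected after randomisation, so equal baseline means are no longer guaranteed.

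The cost is a change of model wording, with no new data. It should be settled before any unblinded analysis, since the article permits interim analyses by an unblinded statistician.
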